#### Fidelity

Whether the PAT was administered as intended will be assessed using monthly EHR data. The coded data captured at Nemours will also allow us to confirm the completion of each PAT in its entirety. The coordinators will meet monthly to problem-solve any concerns about data collection. In the TIER condition, attendance on calls and minutes of the monthly consultation calls will be prepared. The champion will complete a questionnaire at the beginning of the study year, and at 6 and 12 months to document their activities.

### Dissemination toolkit (aim 3)

To broadly disseminate the PAT, a theoretically and data-driven web-based PAT Implementation Toolkit will be developed with the information, resources, and tools necessary to implement the PAT. This corresponds with the Prevention Delivery System of the ISF (develop educational materials, distribute educational materials, purposely re-examine the implementation) [37].

#### Participants

There will be 20 purposively sampled participants from the aim 1 stakeholders (*n* = 10) and from sites that implemented the PAT in aim 2 (*n* = 10 site PIs and champions). Cognitive interviews will be conducted to ascertain their interpretation and understanding of the PAT Implementation Toolkit. This sample size is consistent with the PROMIS methods [55] and the past experience of the research team [56].

#### Procedure

Subsequent to the final analysis of data from the aim 2 trial, we will refine the preliminary framework for the PAT Implementation Toolkit website which we expect will include the training webinar, technology support, PAT Implementation Plan, complete information to implement the PAT across centers of different sizes, materials specific to using the Spanish version of the PAT, suggestions for overcoming identified barriers and bolstering facilitators, evidence for how screening can impact health disparities, frequently asked questions, and guide for sites in identifying resources to guide intervention based on PAT scores. The Toolkit will be web-based and easily accessible.

#### Cognitive interviews

Qualitative, think-aloud interviews [57] will be conducted by video conference using a semi-structured interview guide. During this audio-recorded interview, providers “walk through” the web-based PAT Implementation Toolkit to identify areas for clarification and improvement. Interviews will be transcribed by a professional transcription service and uploaded to a qualitative data management program (Atlas.ti ©) for formal coding.

#### Dissemination

The Agency for Healthcare Research and Quality Publishing and Communications Guidelines (https://www.ahrq.gov/research/publications/pubcomguide/index.html) will guide dissemination. We will coordinate with Children’s Oncology Group (COG) to assure sites have access to the Toolkit. We will contact all sites in the PIPS-CSS study to support their use of the Toolkit. As a site in the National Cancer Institute Community Oncology Research Program (NCORP), we will include a broad network of community and minority sites.

### Data analysis

#### Aim 1

The interviews will be electronically recorded and professionally transcribed. All data will be stored and managed on a secure drive. Data will be inductively analyzed using Atlas.ti ©. Content analytic strategies will be used to identify codes, categories, and themes [58, 59]. Analysis will proceed as the investigators simultaneously collect information through interviews, read each interview as an individual case, consider the topics addressed in the interview guide, disassemble each interview through coding with preliminary codes, define and combine codes into categories and categories into themes, and consider data from each category across all cases [60].

We will first independently code three interviews selected to represent different stakeholders (patient/family, providers, and institution) to define an initial set of codes and codebook. Study coordinators will be trained to manage and analyze qualitative data [61–63] and supervised by an expert qualitative researcher. The investigators will independently code five interviews. For the remaining interviews, each transcript will be coded independently by a two-person team that will discuss each interview and reconcile any discrepancies until they reach 75% agreement. After this point, interviews will be coded independently but will be reviewed and discussed if a discrepancy is found. The investigators will review all the coded transcripts. As coding continues, codes will be combined into categories. Finally, all data will be examined in each category to combine categories into themes. The themes will be translated into content of the PAT webinar for strategy I and enhanced strategies included in strategy II with attention to health disparities and barriers and facilitators at the patient/family, provider, and institution levels. The rigor of the iterative analytic process will follow standards for qualitative research [63, 64].

#### Aim 2

PAT implementation will be tested using a head-to-head randomized implementation (comparative effectiveness of two implementation strategies) trial in three cohorts over 3 years. *Randomization*. Eighteen sites will be randomized to one of three cohorts. Each cohort will be further randomized to one of the two strategy conditions. Randomization will stratify sites by size to maximize internal validity and statistical power. Sites will be randomized by a data analyst not connected with the study using a two-step Excel = RAND() function. The sequence will be stored in a password-protected electronic file. *Sample size*. The estimated sample of patients/families is based on the median number of new patients each year from the PIPS-CSS database: small (*n* = 60), medium (*n* = 92), large (*n* = 339) multiplied by 6 sites at each size, a total of 2946, with 1473 families allocated to each strategy. With an anticipated Interclass Correlation Coefficient (ICC) [65] of .005, the effective sample size is 950 per arm, a sample size that is sufficient to detect a small effect between the two strategies given 80% power (alpha = .05, one sided). We project a Hispanic sample of 20% of the total (*n* = 589). Based on our research [8], approximately 30% of Hispanic caregivers will be more acculturated/not literate in Spanish at the level necessary to complete the Spanish PAT, rendering a sample of 412. With an anticipated ICC of .005, the effective sample size is 224 which is sufficient to detect a medium effective between the English and Spanish versions given 80% power (alpha = .05, one sided). At the provider level, each of 18 sites has a PI and up to four people screening, and for TIER sites, a champion. Therefore the staff sample ranges from a minimum of 45 ([18 × 2] + 9) to a maximum of 99 ([18 × 5] + 9), likely in the middle given the range of size of sites. At the institution level, 18 sites will be randomly assigned to one of two strategies (9 sites/group). These sample sizes are comparable to other implementation science studies [66].

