**Method:**

The PAT will be implemented across a national sample of 18 pediatric cancer programs ranging in size (annual new patients) in a mixed methods, comparative effectiveness study, guided by the Interactive Systems Framework for Dissemination and Implementation, comparing two implementation strategies. It is hypothesized that implementation will be more successful at the patient/family, provider, and institutional level when training (strategy I) is combined with implementation expanded resources (strategy II). There are three aims: (1) Refine the two implementation strategies using semi-structured qualitative interviews with 19 stakeholders including parent advocates, providers, pediatric oncology organization representatives, healthcare industry leaders; (2) Compare the two theoretically based and empirically informed strategies to implement the PAT in English and Spanish using a cluster-randomized controlled trial across 18 sites. Stratified by size, sites will be randomized to cohort (3) and strategy (2). Outcomes include adoption and penetration of screening (patient/family), staff job satisfaction/burnout (provider), and cost-effective use of resources consistent with family risk (institution); (3) Based on the results of the trial and feedback from the first and second aim, we will develop and disseminate a web-based PAT Implementation Toolkit.

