### Specific aims

Based on the Interactive Systems Framework for Dissemination and Implementation (ISF) [36], there are three stages in this mixed methods research (Fig. 2). First, two implementation strategies [37], to improve integration of the PAT into standard pediatric cancer care, will be refined using feedback from 19 stakeholders (qualitative methods). The strategies are based on prior PAT studies, the dissemination and implementation literature [37], and Social Ecological [38] and Pediatric Psychosocial Preventative Health Models [19]. Strategy I is training (webinar) to educate providers on the PAT and its administration. Strategy II is Training + Implementation Expanded Resources (TIER), which augments training with consultation calls and identification of a site champion. Second, we will conduct a comparative effectiveness trial of the two strategies at 18 childhood cancer centers of three sizes examining family (penetration, health equity), provider (feasibility, acceptability, burnout, and job satisfaction), and institution (adoption, sustainability, costs) implementation outcomes [39]. We will randomize sites to time of implementation (three cohorts) and strategy (two—I, II). Third, we will develop and disseminate a web-based PAT Implementation Toolkit for family psychosocial risk screening in pediatric cancer.

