### Cluster-randomized comparative effectiveness trial (aim 2)

PAT implementation will be tested using a head-to-head randomized implementation (comparative effectiveness of two implementation strategies) trial initiated in three cohorts of 1 year each (2021, 2022, 2023). All 18 pediatric cancer programs invited to participate in the trial agreed to a 2-step randomization process stratified by size of site; sites will be randomized to one of three cohorts and then to strategy, comparing strategy I (training) with strategy II (TIER).

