#### Strategy II

Strategy II includes the webinar and technical support as above with the addition of two evidence-based resources that may improve implementation. The site PI and center staff conducting screening will participate in a monthly 1-h consultation call (provide ongoing consultation, create a learning collaborative) with other TIER sites in that cohort. The group format of this strategy is intended to foster group problem-solving and peer support about issues in implementation. Sites will identify a champion (identify and prepare champions) who will advocate for PAT implementation and support staff in screening activities by serving as a resource to problem-solve and communicate with the broader clinical staff about screening and psychosocial risk. The champion will likely be a clinical leader with enthusiasm and commitment to universal psychosocial risk screening.

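### One sentence of the randomisation paragraph makes the cohort, not the site, the unit assigned to a strategy, which contradicts the plan's own 9-versus-9 site allocation

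*Protocol article*

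**What the plan says.** The randomisation paragraph (Data analysis, Aim 2) describes two steps. The first is "Eighteen sites will be randomized to one of three cohorts". The second is "Each cohort will be further randomized to one of the two strategy conditions". The paragraph then says that sites are stratified by size and that an independent analyst makes a two-step draw of sites.

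Everything else on the unit of assignment points to the site:

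- Abstract, Method: "Stratified by size, sites will be randomized to cohort (3) and strategy (2".
- Specific aims: "We will randomize sites to time of implementation (three cohorts) and strategy".
- Aim 2 trial section, which also sets out the two-step process: "sites will be randomized to one of three cohorts and then to strategy".
- Sample size text, in the same paragraph as the disputed sentence: "18 sites will be randomly assigned to one of two strategies (9 sites/group". It also gives 1473 families per strategy, and 45 to 99 staff on the basis of nine TIER sites with a champion.
- Strategy II: the monthly call is held "with other TIER sites in that cohort", which reads most naturally as a cohort holding sites of both strategies.
- Data cleaning and missing data: cohort and program size are to be examined and, where necessary, adjusted for.

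**The concern.** The sentence is an affirmative statement of how strategy is assigned, in the paragraph that governs the draw. Taken at its word, every site in a cohort receives the same strategy. There would then be three units of randomisation instead of 18. Strategy would be tied to the start years 2021, 2022 and 2023, so any change over time in staffing or screening practice could not be told apart from the effect of TIER. The planned adjustment for cohort could not be carried out.

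The draw is given to an analyst outside the study, who would rely on the written rule. Later readers also need that rule to know what was randomised.

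**Working it through.** **Inputs.** All come from the Protocol article.

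- 18 sites, six in each of three size categories (Selection of sites).
- Three cohorts of one year each (Aim 2 trial section).
- Median new patients per year of 60, 92 and 339 for small, medium and large sites (Sample size).
- Staff per site: a PI plus one to four screeners, and one champion per TIER site (Sample size).
- Assumption: six sites per cohort, two of each size. Stratifying six sites per size over three cohorts implies this, but it is not printed.

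**Step 1: the plan's own figures under site-level randomisation.** Three sizes × three cohorts × two strategies = 18 cells, one site per cell.

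- Sites per strategy: 3 × 3 = 9.
- Families in total: 6 × (60 + 92 + 339) = 6 × 491 = 2946.
- Families per strategy: 3 × 491 = 1473.
- Staff: 18 × 2 + 9 = 45 to 18 × 5 + 9 = 99.

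All the stated allocation figures reproduce.

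**Step 2: the same figures under the literal sentence.** Each of three cohorts takes one of two strategies, so there are 2³ = 8 assignments. TIER receives 6 × (number of cohorts assigned to TIER) sites. Families per cohort are 2 × 491 = 982.

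| Cohorts on TIER | Assignments (of 8) | TIER / training sites | TIER / training families | Staff range |
|---|---|---|---|---|
| 0 | 1 | 0 / 18 | 0 / 2946 | 36 to 90 |
| 1 | 3 | 6 / 12 | 982 / 1964 | 42 to 96 |
| 2 | 3 | 12 / 6 | 1964 / 982 | 48 to 102 |
| 3 | 1 | 18 / 0 | 2946 / 0 | 54 to 108 |
| Stated in the plan | | 9 / 9 | 1473 / 1473 | 45 to 99 |

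No row matches the plan. In two of the eight assignments there is no comparison at all.

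**Step 3: can strategy be separated from cohort?** Take a model with an intercept, two cohort indicators C2 and C3, and a strategy indicator S. If the three cohorts have strategies s1, s2 and s3, then S = s1 + (s2 − s1)·C2 + (s3 − s1)·C3. S is an exact combination of the other columns. The design matrix has rank 3 of 4 in all eight assignments, so no strategy effect can be estimated after adjusting for cohort. With three sites on each strategy in every cohort, the rank is 4 and both effects can be estimated.

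**Step 4: sensitivity to the cohort-size assumption.** Whole-cohort assignment could reach 9/9 with unequal cohorts, for example if one cohort held exactly nine sites. That does not fit six sites per size spread evenly over three cohorts. It would also leave strategy nested in cohort, as in step 3.

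**The case against.** The strongest reply is that this is loose wording and not the design. The abstract, the Specific aims, the Aim 2 trial section and two other sentences of the same paragraph make the site the unit. The Aim 2 trial section states the unit of each step without ambiguity. The within-cohort TIER calls and the planned cohort adjustment both fit best with mixed cohorts. On this view the sentence is shorthand for randomising the sites within each cohort. That stands as an account of intent. It does not remove the error, because the sentence is a stated allocation rule and not a detail left out of a condensed article.

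Two stronger readings are tempting, and the documents do not support either.

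- A reader might infer that the trial plans to randomise whole cohorts and is confounded with calendar year. That follows only if one sentence is obeyed against all the others.
- A reader might infer that strategy will be badly unbalanced within cohorts, because size is the only stratum named. Suppose strategy were drawn within size alone (three of six sites per size to TIER, two sites per size in each cohort). All three cohorts would then split 3/3 in 14.8% of draws, and some cohort would have one or no TIER site in 24.0%. But the sequence of cohort first and strategy second does not clearly describe such a draw. A condensed article may also leave within-cohort balance to the full protocol. These figures only illustrate why it helps to state the balance when the sentence is corrected.

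**Conclusion.** The sentence is wrong as written and should be corrected. It contradicts three other parts of the article and, given six sites per cohort, cannot produce the 9 sites per group, 1473 families per strategy or 45 to 99 staff stated in its own paragraph. Followed literally, it would leave three units of randomisation and make strategy inseparable from start year.

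The point goes no further than that. Site-level randomisation is the evident intent, it reproduces every stated allocation figure, and nothing here shows that the intended design is confounded. The split figures rest on equal cohorts of six, which the article implies but does not state.

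**What to change.** Replace the sentence with: *Within each size category, two sites are randomised to each cohort; within each size-by-cohort pair, one site is randomised to Strategy I and the other to Strategy II, both being assigned and told at the same time.*

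This gives nine pairs, 3/3 in each cohort and 9/9 overall. It keeps 1473 expected families per strategy and 45 to 99 staff, leaves strategy separable from cohort, and puts three TIER sites in every cohort for the group calls.

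The cost is one sentence, with the same sites, the same independent analyst and the same two-step draw. The small downside is that the second site of each pair is determined by the first, which assigning and telling both together handles. If the draw has already been made, the sentence should instead record the procedure that was actually used.

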#### Selection of sites

The following criteria were used in site selection:
*Provide staff and tablet computer for screening*. Each site agreed to provide the staff person(s) screening and tablets. Each site will be provided support for a portion of the site PI’s effort and a part-time research coordinator based on center size for purposes of research only (the research coordinator will not do the screening).*Center size*. Because program size is related to the size of the psychosocial team and related psychosocial resources [5], we used PIPS-CSS data to stratify by size to obtain three equal and clinically relevant groups based on number of new pediatric cancer patients annually—small (30–60), medium (61–149), and large (150+). We selected 6 sites for each of the three size categories.*Psychosocial staff*. To assure that there are staff to conduct screening and act on the results of screening, selected sites are at or above the median for the size of their psychosocial team (number [full time equivalents] social workers + psychologists + psychiatrists + child life specialists) [5] based on PIPS-CSS data.*Diversity of population*. We selected centers in states with a high percentage of ethnic or racial minority families and/or families with socioeconomic disadvantage. CA, TX, FL, NY, and NJ have large Hispanic populations [42]. AL, NC, and VA have the most rapidly increasing Hispanic populations, and AL, LA, NC, and VA have the largest percentage of African-Americans [43]. Thirteen out of 18 sites are in these states. Twelve out of 18 are in states with > 20% of children living in poverty [44]. Other sites were selected to balance geography, race, ethnicity, and SES.

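### The stated effective sample sizes (950 per arm; 224 for the Spanish sample) do not follow from the protocol's own family counts, site counts and ICC of .005

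*Protocol article*

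**What the plan says.** All of this is in the protocol article, Data analysis, Aim 2, under sample size.

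- Families are projected from site medians: "small (*n* = 60), medium (*n* = 92), large (*n* = 339) multiplied by 6 sites at each size, a total of 2946". Half of that number, 1473, is assigned to each arm.
- Sites: "18 sites will be randomly assigned to one of two strategies (9 sites/group"). On allocation: "Randomization will stratify sites by size to maximize internal validity and statistical power".
- Strategy comparison: "With an anticipated Interclass Correlation Coefficient (ICC) [65] of .005, the effective sample size is 950 per arm". This is said to be enough for a small effect at 80% power, one-sided alpha .05.
- Spanish sample: 20% of the total is projected to be Hispanic (589), and about 30% of these are set aside as unable to complete the Spanish version, which leaves 412. Then: "With an anticipated ICC of .005, the effective sample size is 224". This is said to be enough for a medium effect between the language versions at the same power and alpha.

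The paragraph gives no cluster size, design effect or formula for either effective size, and no number for a small or medium effect.

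**The concern.** The two effective sizes are the only clustering-adjusted figures behind the two family-level power statements. The inputs, the ICC and the results are all printed, so a reader can check the step between them, and it does not check.

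The two figures also disagree with each other. At the same ICC and the same sites, 950 implies a design effect of 1.55 and 224 implies 1.84. The Spanish families are about one-seventh of all families, so their clusters should be smaller and their design effect lower, yet it is the higher of the two.

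At stake is whether the stated information for strategy I against TIER can be relied on. The H2.1 analysis is to adjust for clustering using ICCs, so the planning figure should rest on a design effect that can be reproduced.

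**Working it through.** **Raw counts (these reproduce).** (60 + 92 + 339) × 6 = 2946; 2946 / 2 = 1473; 0.20 × 2946 = 589; 0.70 × 589 = 412. The fault is confined to the clustering step.

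**Strategy comparison.** Inputs: N = 1473 per arm, 9 sites per arm, ICC = .005, site sizes 60, 92 and 339. Three sites of each size per arm is an assumption, drawn from the stratification by size; it matches the stated total, since 3 × 491 = 1473.

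1. Equal sites. Mean size m = 1473 / 9 = 163.67. Design effect (DE) = 1 + (m − 1) × ICC = 1 + 162.67 × .005 = 1.813. Effective size = 1473 / 1.813 = **812**.
2. Site by site. Sum n / [1 + (n − 1) × .005]: 60 / 1.295 = 46.3; 92 / 1.455 = 63.2; 339 / 2.690 = 126.0. Three times the total of 235.6 is **707**.
3. Variation in site size (CV/Kish). CV² = 0.580. DE = 1 + [(1 + 0.580) × 163.67 − 1] × .005 = 2.288. Effective size = 1473 / 2.288 = **644**.

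Working back from 950: DE = 1473 / 950 = 1.551, so m = 0.551 / .005 + 1 = 111 families per site; or, at m = 163.67, ICC = 0.551 / 162.67 = .0034. The protocol states neither.

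Other choices also miss 950: median site size of 92 gives 1012, harmonic mean (98.4) 991, geometric mean (123.2) 914, 1473 spread over 18 sites 1049, and 2946 over six cells of 491 gives 854.

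Overstatement: 950 / 812 = 1.17; 950 / 707 = 1.34; 950 / 644 = 1.48.

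**Spanish sample.** Inputs: 412 families, 18 sites, ICC = .005. The distribution over sites is not stated, so each line below carries an assumption.

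| Assumed distribution | Calculation | Effective size |
|---|---|---|
| Even over 18 sites | m = 22.9; DE = 1.109 | 371 |
| Proportional to site size, site by site | sizes 8.4, 12.9, 47.5 | 353 |
| Proportional, CV/Kish | DE = 1.176 | 350 |
| Six sites only | m = 68.7; DE = 1.338 | 308 |
| Three sites only | m = 137.3; DE = 1.682 | 245 |
| Two sites only | m = 206; DE = 2.025 | 203 |

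Working back from 224: DE = 412 / 224 = 1.839, so m = 0.839 / .005 + 1 = 169 per site. That is close to the full-site mean of 163.67, and 412 / 1.813 = 227. The likely explanation is that the full-site design effect was applied to the Spanish subset. As a cross-check, the same design effect of 1.839 applied to 1473 gives 801, not 950.

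**Effect on power.** Normal approximation, one-sided .05, 80% power: minimum detectable d = √(2/n) × (1.645 + 0.842).

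| n per arm | Minimum detectable d | Power for d = 0.2 |
|---|---|---|
| 950 | 0.114 | 99.7% |
| 812 | 0.123 | 99.1% |
| 707 | 0.132 | 98.3% |
| 644 | 0.139 | 97.4% |

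Needed for d = 0.2: 2 × 2.487² / 0.04, about 310 per arm. Needed for d = 0.5: 2 × 2.487² / 0.25, about 50 per group. Even if the stated 224 were both language groups together, 112 per group exceeds 50.

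**The case against.** The strongest reply is that nothing the protocol concludes changes. It claims only that the samples suffice for a small and a medium effect. With d = 0.2 and 0.5, both claims hold at every corrected figure, and the Spanish error is conservative. This stands. A reader might infer from an overstated effective size that the trial is underpowered; at ICC .005 the documents do not support that.

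A second reply is that the two design effects can coexist. A reader might call it impossible for the smaller clusters to have the larger design effect. That goes too far. Selection of sites says centers were chosen partly from states with large or fast-growing Hispanic populations, and the protocol does not say how Spanish-version families are distributed. About two or three sites holding all 412 would give 224. The protocol describes no such concentration, and it places 13 of 18 sites in the named diverse states, so this is unlikely but not excluded.

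Third, 350–371 is not an established replacement. It depends on the assumed distribution and treats the 412 as a stand-alone clustered sample. The comparison is between language versions used at the same sites, so part of the site effect cancels and a different, probably smaller, correction applies. This stands too, and it limits what the fix can prescribe.

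Fourth, there is no single correct per-arm figure when sites are unequal. That is true, but the three standard calculations run from 644 to 812 and all lie well below 950.

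Finally, a reader might take the small-site median of 60 as another error because it equals the upper limit of the 30–60 band. It lies inside the band and comes from a database not reproduced in the article, so the documents do not show it to be wrong. Nothing here depends on it.

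**Conclusion.** The point holds as a correction of stated figures. The per-arm effective size of 950 is overstated by 17% (equal sites), 34% (stated sizes, site by site) or 48% (CV/Kish). The Spanish 224 is about 36–40% below the 350–371 that follows if families are spread evenly or in proportion to site size. The two figures are inconsistent with each other unless Spanish-version families are concentrated in about two or three sites.

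This rests on the protocol's ICC of .005, taken as given; on three sites of each size per arm for the 707 and 644; and on the stated distribution assumptions for the Spanish figure. With small and medium read as d = 0.2 and 0.5, which the protocol does not specify, its sufficiency claims survive.

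**What to change.** In the sample-size paragraph:

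- Restate the per-arm effective size as about 640–810, or about 700 with the stated unequal site sizes, and show the cluster size and design-effect formula used.
- Give the minimum detectable d as about 0.12–0.14 (950 would imply 0.114), and state the numerical effect meant by small and by medium.
- Recompute the Spanish figure from the Spanish per-site cluster size, state how those families are assumed to be distributed over sites, and note that English and Spanish families are compared within sites.

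The cost is one corrected paragraph. The headline effective size becomes less favorable; the number of sites, the design and the sufficiency statements at ICC .005 do not change.
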